### Statistics

#### Analysis of outcome measures

A time to event analysis will be carried out to compare the primary outcome measure for paper-based charting with SEND-based charting. Competing events, such as transfer to theatre or cardiac arrest, may prevent a second set of observations being taken. Common electronically-recorded competing events are listed in Table 1. The time and type of any of these events will be recorded if they occur within 14 h of the triggering set of observations. If another set of observations or a competing event is not found within 14 h from the first triggering observation set it will be assumed that no further observations took place.

The time point of the step and ward will be included as covariates. The study design is multi-level, patients within ward, and a multi-level model will be used to take into account the correlation between patients within ward. Other covariates at the patient and ward level will be included in the models. A detailed statistical analysis plan will be written prior to analysis, however it is expected that the method for the primary outcome will be in the form of a semi-parametric random effects model, such as those described by Scheike et al. [31] and Zhou et al. [32].

Secondary endpoints will be reported for each period ward combination. A patient may be admitted to ICU more than once, but only the first ICU admission will be considered for the analysis. For each period-ward combination the probability of admission to ICU will be calculated from the number of patients admitted to ICU at least once and the total number of patients.

### Sample size

The number of patients included in the study will primarily be pragmatic. All eligible admissions will be included for the first hospitals. A subsequent interim analysis will determine what proportion of eligible admissions within a study ward in the paper charting cohort will be included for the final hospital, the largest of the four institutions. If the analysis determines that fewer than 100 % of admissions are required then admissions will be randomly selected. All eligible admissions where data is recorded using SEND will be included for all four hospitals. We anticipate that the total number of admissions included in the study will be around 60,000.

Power calculation for the first hospital is based upon analysis of (currently unpublished) data from a previous trial conducted locally. We assume that the proportion of patients who have a further observation within three hours of a recording an EWS ≥3 will be 0.5 in the paper arm (as seen in a previous study) and 0.6 in the electronic arm, that there will be an average of 11 patients with an initial EWS ≥3 per cell, and conservatively that the intra-cluster correlation (ICC) will be 0.15, the power is estimated to be 79.3 % for a 5 % alpha level.

This calculation depends on statistics estimated from the one small study. However it does indicate that when including all four hospitals the study will be sufficiently powerful to detect a difference of 10 % in the primary outcome between groups.

### Compensation for potential biases

#### Lack of randomisation

In a conventional stepped wedge randomised control trial design the order in which the clusters ‘switched’ treatment would be randomly chosen. Randomisation is not feasible here as the order and timing of roll out is dictated by operational factors and clinical risk. We do not consider this to be a significant limitation as it is unclear how a lack of randomisation in this design could manipulate results to favour either of the treatments.

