### SEND Implementation Plan

SEND will be used for the recording of routine observations on all adult wards and day units except for obstetrics wards and intensive care units (ICUs). A different EWS is used on obstetric wards and the ICUs already have an electronic charting system integrated into their patient record system.

Deployment on each ward is a five week procedure, consisting of 3 weeks of preparation followed by two weeks of enhanced support following the date the system is activated on the ward. (Fig. 3) During the enhanced support weeks project staff are available on the ward to identify problems and offer additional training to users. In some cases it will be necessary to roll out groups of related wards simultaneously to ensure patient care is not compromised. Roll-out is planned to commence on a new ward (or group of wards) every fortnight. However, it is anticipated that practical difficulties may prevent this occurring in all cases. The sequence of ward roll-out is determined by pragmatic and patient safety considerations rather than being randomised.

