#### Heterogeneity of patients between wards

Patients with similar characteristics are likely to be clustered within wards. Similarly wards of a similar type are clustered within the hospital sites. There is a risk that variation in outcomes between clusters may be large, limiting the inferences that can be made. The stepped-wedge design addresses this issue as it enables both between-cluster comparisons and within-cluster comparisons to be made. Further compensation will be provided by using ward level and patient level characteristics as covariates in the analysis.

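### The protocol dismisses non-random ward order as a limitation while naming clinical risk as a driver of it; a random ward effect could pass a modest part of any resulting ward difference into the SEND estimate, and a fixed ward effect would stop this cheaply

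*Protocol article*

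**What the plan says.** Four parts of the protocol article bear on this.

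- **What sets the order.** Under Lack of randomisation, "the order and timing of roll out is dictated by operational factors and clinical risk". The SEND Implementation Plan agrees: "The sequence of ward roll-out is determined by pragmatic and patient safety considerations rather than being randomised".
- **What is concluded from it.** The same paragraph on randomisation judges that this is no significant limitation, on the ground that "it is unclear how a lack of randomisation in this design could manipulate results to favour either of the treatments".
- **Which comparisons are used.** Under Heterogeneity of patients between wards, the design is said to help because "it enables both between-cluster comparisons and within-cluster comparisons to be made", and "Further compensation will be provided by using ward level and patient level characteristics as covariates in the analysis".
- **Which model is planned.** Under Analysis of outcome measures, "The time point of the step and ward will be included as covariates", a multi-level model is to handle correlation within ward, and "it is expected that the method for the primary outcome will be in the form of a semi-parametric random effects model". The details are left to an analysis plan that is not shown.

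**The concern.** A random ward effect treats a ward's underlying level as unrelated to when that ward receives SEND. Randomising the order would secure this by design. Here the order is chosen, and one stated reason for the choice is clinical risk. Trust policy, as described under Hypothesis, ties how soon observations are repeated to patient risk, so a relation between a ward's risk and its baseline timeliness is plausible.

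In a wedge, early wards contribute proportionately more SEND data and late wards more paper data. If early wards start out better, the between-ward comparison flatters SEND; if they start out worse, it counts against SEND. That comparison is one of the two that the heterogeneity paragraph welcomes as a strength.

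Two things are at stake: a possible shift in the primary estimate, and a reassurance that would probably be carried into the report. The Discussion goes as far as to say that a properly analysed stepped wedge comes close to a randomised trial in quality of evidence.

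**Working it through.** **Inputs from the protocol article.** Sample size: 0.5 (paper) and 0.6 (SEND) re-observed within three hours, 11 patients per ward-period cell, ICC 0.15, power 79.3% at 5% alpha. SEND Implementation Plan: one step per fortnight. Delayed Effect of intervention: three further months at each site, about six fortnights.

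**Assumptions.** The number of wards in the first hospital, *I*, is not given; 8 to 12 is used, with one ward per step and one baseline fortnight, so *T* = *I* + 7 periods. Alpha is taken as two-sided. ICCs of 0.05 and 0.02 are added as a range because 0.15 is called conservative. The calculation uses the three-hour binary outcome of the power calculation, not the time-to-event model.

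**The plan's own figure.** With a random ward intercept and fixed period effects, power is 77.4% for 11 wards and 83.6% for 12. The stated 79.3% lies between these. It cannot be checked exactly, but it is attainable and is not shown to be wrong.

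**Formulas.** Let v = 0.55 × 0.45 = 0.2475.

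- Between-ward variance: τ² = ICC × v. Cell error variance: s² = (1 − ICC) × v / 11.
- Weight on between-ward information: ψ = s² / (s² + Tτ²).
- Between-ward sum of squares of exposure: B = (I³ − I) / (12T).
- Within-ward sum of squares, after period effects: W = (I² − 1)/6 − B.
- Random-ward SE = √[s² / (W + ψB)]; fixed-ward SE = √[s² / W].
- If ward level is exactly linear in order with SD τ, the between-ward slope is β = τ / √[B/(IT)], and the bias is ψBβ / (W + ψB). With fixed ward effects ψ = 0, so the bias is 0.

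**Worked case: I = 12, T = 19, ICC 0.15.**

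- τ² = 0.0371, so τ = 0.193; s² = 0.0191; ψ = 0.0191 / (0.0191 + 19 × 0.0371) = 0.0264.
- B = 1716 / 228 = 7.53; W = 143/6 − 7.53 = 16.31; ψB = 0.199.
- β = 0.193 / √[7.53 / (12 × 19)] = 1.06.
- Bias = 0.199 × 1.06 / 16.51 = 0.0128.
- Random-ward SE = 0.0340; fixed-ward SE = 0.0342, larger by √(16.51/16.31) − 1 = 0.6%.
- With no true effect, bias/SE = 0.375, so the type I error is Φ(−1.585) + Φ(−2.335) = 6.6%.

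**Range over 8 to 12 wards, six follow-up fortnights, perfect alignment.**

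| ICC | Bias, random ward | Type I error | Bias, fixed ward | SE increase, fixed ward |
|---|---|---|---|---|
| 0.15 (protocol) | 0.013–0.015 | 6.1–6.6% | 0 | 0.6% |
| 0.05 (assumed) | 0.023–0.026 | 8.0–9.8% | 0 | about 2% |
| 0.02 (assumed) | 0.031–0.035 | 10.6–14.3% | 0 | about 4% |

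Bias is proportional to the correlation between ward level and order, so a correlation of 0.5 halves every bias figure. A smaller ICC gives a larger bias because the model then leans more on between-ward information (ψ rises).

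**What a fixed ward effect does not cure.** As an illustration, let wards have their own linear trends, from +1 percentage point per fortnight in the first ward to −1 in the last. With six follow-up fortnights the fixed-ward estimate is biased by about −0.047. In the symmetric wedge without extra follow-up the same trends give zero bias.

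**The case against.** The defence has several sound points.

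- **The wording is cautious.** A reader might infer that the protocol claims non-random order cannot favour either arm. It says only that the route is unclear. What remains open to criticism is the step from unclear to not a significant limitation.
- **The plan does not rest on between-ward comparison alone.** It also relies on within-ward comparison and on ward and patient covariates. This stands, although covariates help only where they capture what drove the order.
- **The model is not settled.** A reader might infer that the planned analysis is certain to carry the confounding. The documents do not support that: the random effects form is only expected, ward is also named as a covariate, and a fixed ward term would close this route for differences that are constant over time. Leaving the coding of ward to the analysis plan is no fault in itself. The point lies in the position the protocol does state and in the model it says it expects.
- **The link is assumed.** Nothing in the protocol shows that early and late wards differ in baseline timeliness. Operational reasons may dominate, and these may be unrelated to it.
- **The size is modest.** Without follow-up and with 8 wards, the worst case at ICC 0.15 would be 0.031. The protocol commits to three further months at each site, so that larger figure should not be used.

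One counter-argument carries less weight: that the fix is partial. Order-related trends can bias either model, so they are no reason to leave the time-constant part in.

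**Conclusion.** The reassurance about non-random order is not supported, because the protocol itself names a driver of order through which bias could arise. The bias is possible in either direction; it is neither certain nor shown. At the protocol's ICC, with the planned follow-up and 8 to 12 wards, even perfect alignment of ward level with order shifts the estimate by 0.013 to 0.015, which is 13% to 15% of the 0.10 target, and raises the type I error to between 6% and 7%. The shift is two to three times as large if the ICC is nearer 0.02.

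These figures rest on an assumed number of wards, a linear worst case and the three-hour binary form of the outcome. The point is worth correcting because the remedy costs little, not because the primary result is likely to be overturned.

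**What to change.** 1. In the primary model, enter ward as a fixed effect, or stratify the baseline hazard by ward, together with period effects, so that the SEND estimate rests on change within wards. Keep the random-ward model as a sensitivity analysis.
2. Replace the reassurance under Lack of randomisation with a statement that non-random order may confound the comparison, and that ward-specific time trends related to order remain a limitation even with fixed ward effects.
3. Report baseline ward characteristics by roll-out order, so that readers can judge whether early and late wards differed.

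**Cost.** These are changes of wording and model specification, with no new data design. The standard error rises by about 0.6% at ICC 0.15, 2% at 0.05 and 4% at 0.02. For 12 wards at ICC 0.15 with follow-up, power moves from 83.6% to 83.2%. Each ward would supply about 11 × 15 = 165 to 11 × 19 = 209 patients under the planning assumptions, enough to support its own term or stratum.

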#### Delayed Effect of intervention

It is possible that the effect of the intervention may increase as staff become more familiar with this system. Therefore the peak effect may be delayed for some weeks after roll out. This will reduce the power of the study. Additional follow-up time is a recognised method of compensating for this issue [33]. We will continue data collection for a further 3 months after completion of the last ward roll out at each site. Additional analyses will investigate whether the treatment effect changes with time from implementation of SEND.

#### Heterogeneity of patients between wards

Patients with similar characteristics are likely to be clustered within wards. Similarly wards of a similar type are clustered within the hospital sites. There is a risk that variation in outcomes between clusters may be large, limiting the inferences that can be made. The stepped-wedge design addresses this issue as it enables both between-cluster comparisons and within-cluster comparisons to be made. Further compensation will be provided by using ward level and patient level characteristics as covariates in the analysis.

#### External factors and time trends

External factors such as seasonal changes in workload may confound the outcomes. These are mitigated to some degree by the study design and data analysis which will include a time period covariate. The temporal variation of individual ward and patient level covariates can also be modelled.

#### Recurrent patient admissions

Patients may have more than one admission episode. For the purpose of the primary outcome the unit of analysis will be patient episodes rather than patients and we will treat multiple episodes within the same patient as independent. Timely recording of vital signs seems unlikely to be correlated with patient characteristics.

## Discussion

Measuring the effect of implementing a novel clinical information system is challenging. The practicalities of rolling out a system safely and effectively rarely permit a randomised study. The before-and-after design, which has been used frequently in the past, is subject to bias from confounding variables. We hope this study will provide a model for others to follow in the future.

The stepped-wedge design is well suited to the study of a phased roll-out. If properly analysed, adjusting for time and other confounding variables, the quality of evidence from a stepped wedge trial approaches that of a randomised controlled trial [34]. The best methods of modelling the data remain a subject for debate [35]. We will explore different approaches as part of our analysis.

The best metric to use for the primary endpoint is also challenging. Previous studies have used mortality and length of stay. We find it implausible that the introduction of a new charting system could significantly affect these endpoints alone. Length of stay, in particular, is affected by many external factors. Therefore we report these as secondary endpoints.

The incidence of admission to ICU is a measure related to patient deterioration but its interpretation is unclear. A rise in referrals may either indicate an increased awareness of patient deterioration or it may indicate an increased incidence of deterioration. It is also confounded by the fact that behavioural and systemic factors may inhibit admission to ICU, even if deterioration is recognised.

Our chosen metric, the time from the first triggering observation set to the subsequent observation set, has the benefit of being easy to measure on both paper and electronic charting systems. In contrast to ICU referral, the factors influencing the timing of the second set of observations are largely within the control of the attending nurse.

We have not chosen to measure the response to every triggering observation set as we anticipate that nursing behaviour will change to repeated alerts from an individual patient. Repeated alerting may indicate failure to adequately to treat deterioration but it may also reflect that some treatments take many hours to have an effect. In the latter situation gradually decreasing the frequency of observations may be appropriate.

We have designed our study based on the advice provided by the Agency for Healthcare Research and Quality (AHRQ) Health Information Technology Evaluation Toolkit [36]. This emphasises: (i) the benefits of mixed methods studies and (ii) the need to constrain the range of evaluation metrics to those deemed to be the most important.

We have chosen clinical effectiveness as the main focus of this study. However, it is not the only relevant outcome. Delone and McLeans’s Model of Information System Success [37] lists four determinants of success: system quality, information quality, service quality and user satisfaction. The user questionnaire will allow investigation of each of these aspects. In parallel to this trial we are conducting an investigation of the effects of SEND on nursing workload and a qualitative study of how SEND affects nurses’ ability to deliver care. These will be published separately.

Greenhalgh et al. [38] have highlighted that the effectiveness of a system cannot be divorced from the organisational and cultural setting in which it is implemented. For a description of the organisational culture within our hospitals we refer the reader to the work by Ovseiko et al. [39]. We will also provide descriptors of the hospitals and their case mix to allow readers to compare with their own institutions. By triangulating these sources of data we envisage that readers will be able to draw useful conclusions about how SEND might function in other environments.

## Ethics, consent and permissions

The study protocol was reviewed by the Trust’s Research and Development department and, based upon Healthcare Quality Improvement Partnership guidelines was deemed to be a service evaluation, not requiring review by the National Research Ethics Service. As patient data will be collected without their consent, permissions were obtained from Trust’s Caldicott Guardian and Medical Director in accordance with the Health Research Authority Confidentiality Advisory Group guidelines.

## Abbreviations

APACHE II: acute physiology and chronic health evaluation ii
CEWS: centile-based early warning score
EWS: early warning score
ICNARC: intensive care national audit and research centre
ICU: intensive care unit
OUH: Oxford University Hospitals
PAS: patient administration system
SEND: system for electronic notification and documentation
SUS: system usability scale
